**Contact: [contact]**

1. **Backgrounds**

**3.1 Dementia**

Population projections by the Ministry of Internal Affairs and Communications report that the ageing rate may reach 38.4% by 2065, with approximately 1 in 2.6 people aged 65 or older and 1 in 4 people aged 75 or older. The number of elderly people with dementia is also expected to increase accordingly, and it is estimated that in 2025 the number of elderly people aged 65 and over with dementia will be approximately 7 million, or one in five people.^1)^ Measures for the elderly with dementia will continue to be an ongoing challenge in Japan. However, at present, the effectiveness of drugs to treat dementia is extremely limited, and much is expected from non-pharmacological therapies and preventive measures. Under these circumstances, the long-term care insurance service 'short-term intensive rehabilitation for dementia' was introduced in 2006 as rehabilitation for dementia patients, and reports of its effectiveness in improving cognitive functions and peripheral symptoms of dementia are accumulating.^2-5)^ The individualized program of this 'short-term intensive rehabilitation for dementia' is supposed to last at least 20 minutes per session for one person, and it is estimated that it is often carried out for around 20 minutes in real clinical practice. It is necessary to develop effective rehabilitation equipment that can be implemented in about 20 minutes as an individual program for 'short-term intensive rehabilitation for dementia'.

Mild cognitive impairment (MCI) is a concept that describes a condition in which a person presents with mild cognitive impairment that is not normal but not quite dementia and is able to maintain daily life. If the progression from MCI to dementia can be reduced, it may be possible to reduce the prevalence of dementia in the elderly population.

**3.2** A digital application for training abacus-based mental calculations

'SoroTouch' is a digital application for training abacus-based mental calculations developed to help children acquire high calculation skills efficiently in a short period of time. Science-Technology-Engineering-Math (STEM) is an educational model that began in the 2000s in the USA and is a capability that is attracting attention for the development of human resources for the coming era. SoroTouch is an application that aims to acquire the 'time for maths' and 'ability to work through' that will form the basis of STEM in the new era.

**3.3** **Evidence for SoroTouch**

SoroTouch is an iPad application with a unique interface, called 'invisible mode' (where the beads are not displayed), which requires the learner to visualize and manipulate the beads in his/her mind in order to solve the problems. Furthermore, SoroTouch trains fast and accurate manipulation of the beads and has features that facilitate continuous learning. Analysis of learner data showed that 54% of leavers in 2017 and 62% in 2018 had successfully mastered their mental arithmetic skills by the time they left the program. The time spent using SoroTouch for skill acquisition has been validated to fall between 7 and 26 months.^6)^

**3.4 Hypothesis**

Minami et al. have reported on the usefulness of personal computer (PC)-based attention training for patients with higher brain dysfunction in the chronic phase. Twenty-two patients were divided into a PC-based training group and a conventional drill-based attention training group. After a period of two months (eight sessions), the training methods were switched, resulting in a total intervention period of four months. The results showed that the values of the FIM/FAM cognitive items 'Problem Solving', 'Disability Adaptation' and 'Representation', and the behavioral assessment items 'Triggering' and 'Easy Fatigue' improved significantly after the attention training using the PC.^7)^ In the present study, cognitive rehabilitation with the iPad application SoroTouch may improve participants' cognitive functions, and scientific verification through RCTs is desirable.

1. **Objectives**

The present study is an exploratory clinical study. The subjects will be 20 middle-aged and older adults (40-79 years) and the effects on cognitive functions and quality of life (QOL) will be investigated after they perform SoroTouch for 30 minutes a day for 6 months. In the future, it is expected that SoroTouch will prevent dementia in patients with mild cognitive impairment (MCI).

1. **Details of the clinical research**

**5.1　Primary　outcome and secondary outcome**

5.1.1　Primary outcome

Assessment of five cognitive domains by CogEvo®︎: spatial cognition, orientation, memory, attention and executive function.

5.1.2　Secondary outcome

Quality of life assessment using the SF36 questionnaire

Screening for the presence of dementia with the Japanese version of the Montreal Cognitive Assessment (MoCA-J)

**5.2** **Design and outline of the clinical trial**

5.2.1　Design of the clinical trial

1)　Design ：randomized controlled trial

2)　Intervention type: random allocation

3)　Invasive to subjects: no invasive

5.2.2 Clinical research flow/outline

Registration to allocation should be done within 4 weeks. (Assessment allocation period).

Intervention group（n = 10）

**Intervention period （6 months）**

Control group（n = 10）

Enrolment

Informed consent

Random allocation

The principal investigator explains and obtains consent from the study subjects via online tools such as Zoom in order to prevent the spread of COVID-19 infection. The consent forms are converted into PDF format by the staff of the Consortium for Dementia Prevention Activities, and shared on a password-protected Dropbox and sent to the principal investigator. The paper consent forms are then promptly destroyed.

Schedule of the trials

| Evaluation item | **Registration to allocation should be done within 4 weeks. (Assessment allocation period)** | **One month after** | **Two months after** | **Three months after** | **Four months after** | **Five months after** | **Six months after** |
| --- | --- | --- | --- | --- | --- | --- | --- |
| Obtaining consents | ● |  |  |  |  |  |  |
| Investigation of Characteristics | ● |  |  |  |  |  |  |
| **MoCA-J** | ● |  |  |  |  |  | ● |
| SF36 | ● |  |  |  |  |  | ● |
| CogEvo^®︎^ | ● | ● | ● | ● | ● | ● | ● |
| Investigation of adverse events |  | | | | | | |

The participants will conduct the following curriculum in order from J1, as described in the user manual (Ref. 1). The participants will try to complete each stage, which has 30 missions, three aspects in 30 minutes each day.

The learning time is displayed on the SoroTouch recording screen and the learning time and mission completion status are checked by the staff of the Consortium for Dementia Prevention Activities.

If there are participants whose average daily learning time is less than 10 minutes, the data will be analyzed only for the periods when they were able to do more than 10 minutes.

Ref.1 SoroTouch curriculum

**
[figure not shown]
**

**5.3** **Methods of case registration and allocation**

The principal investigator (co-investigator) explains the subject of the study in accordance with the explanatory document and, if consent is obtained, registers and allocates the subject as a research participant. Research participants will be given an identification code for anonymization purposes, which will be used as the identification code for research participants in this study.

The study will be conducted in a randomized comparison to ensure that the allocation does not result in differences in medical background between treatment groups. The participants will be allocated in a 1:1 ratio to the SoroTouch treatment group and the non-treatment group using Muzinwali (https://mujinwari.biz/users/login). The allocation method will be stratified block allocation with CogEvo®︎ (index below and above 70) as allocation factor. After obtaining consent from the study participants, investigators will access Muzinwali to confirm the allocation of the intervention to the study participants concerned. As soon as possible after confirming the allocation, the 'Allocation Instructions/Confirmation Form' is signed and dated. After obtaining consent from the research subject to participate in the research and conducting the allocation, the investigator in charge of the research should ensure that all 'allocation instructions/confirmation forms' are properly kept by the principal investigator.

**5.4** **Medicines-medical devices used in this study**

5.4.1 A digital application for training abacus-based mental calculations ‘SoroTouch’

**5.4.1.1 Functions**

This application has the following functional features.

1. It specializes in the acquisition of imaginative mental calculation skills and is expected to activate the bilateral prefrontal cortex of the cerebrum.
2. The bimanual method is used for effective mental calculation and is expected to activate the bilateral motor areas of the cerebrum.
3. It is an enjoyable application developed by users, which makes it easy to acquire self-learning and maintain motivation.
4. Past studies^6)^ have shown that the system has a proven effect, that over 60% of learners acquire mental arithmetic skills in less than two years.

**5.5** **The expected period of participation of research participants**

From the publication in jRCT to 30 September 2022. It is noted that the trial plan will be published in jRCT after approval by the Showa University School Corporation Clinical Research Review Committee and permission to conduct the research by the head of the implementing medical institution.

**5.6** **Criteria for suspending or discontinuing whole clinical research**

Criteria for suspending or discontinuing the whole clinical trial

If any of the following events occur during the research period, the investigators will discontinue the research on the relevant research participants. When the investigators decide to discontinue or suspend the research, the investigators will take appropriate action to deal with the research participants.

1) When significant information on the quality, safety or efficacy of the equipment used in the study is obtained.

2) When it is deemed difficult to achieve the planned number of cases due to the inability to recruit research participants.

3) When there are instructions from an accredited clinical research review committee to change the research plan, etc., and it is deemed difficult to accept these instructions.

4) When the decision of the accredited clinical research review committee or the administrator of the implementing medical institution instructs to discontinue the research.

5) When a serious or continuous violation of the Clinical Research Act, the Enforcement Regulations or this research protocol occurs.

If the research is to be discontinued, a report will be made to the Authorized Clinical Research Review Committee and the Minister of Health, Labor and Welfare within 10 days of the date of discontinuation. Also, if the research is suspended rather than discontinued, a report will be made to the Authorised Clinical Research Ethics Committee as soon as possible.

**5.7** **How to manage medicines and other products**

Management of the application

This application is to be carried out by the research participants themselves using the iPads loaned by Digika Ltd. The company and the research participant sign a contract based on separate monitoring terms and conditions, and the research participant is responsible for managing the iPad themselves during their participation in the research.

**5.8　Contents directly entered in the case report form and considered source documents**

In this study, the following documents and others are considered source documents (source data).

1) Records of research participant consent and information provided to participants.

2) Information on the presence or absence of diseases, history of diseases, medications taken, etc., as stated in the monitoring application form.

3) Documents or records relating to trials required under the Clinical Research Act in relation to the study.

1. **The inclusion and exclusion criteria and discontinuation criteria for the clinical research**

**6.1** **Target group (diseases)**

　　Middle-aged and elderly adults in the general community

**6.2　 Inclusion criteria**

The subjects must meet all of the following criteria.

1) middle-aged and elderly people who participate in the General Incorporated Association, Consortium for Dementia Prevention Activities.

2) Individuals who are aged between 40 and 79 years when the consent is obtained.

3) Persons who have given their written consent to participate in the study.

［Rationale for setting selection criteria.]

The subjects must be healthy individuals in the age group who are able to continuously carry out SoroTouch.

**6.3　Exclusion criteria**

The subjects must not meet all of the following criteria.

1) Persons with visual or intellectual disabilities that make it difficult to perform SoroTouch.

(2) Persons who have been administered drugs that affect the results of the study to treat dementia or ADHD within six months.

(3) Individuals who are judged to be ineligible by the physician in charge of the study.

[Rationale for setting exclusion criteria.]

(1) Individuals with visual impairment or intellectual disability are difficult to perform the SoroTouch.

(2) Use of drugs that affect cognitive function, as this will affect the results of the study.

3) People who are clearly clinically inappropriate to participate in the study should not participate.

**6.4　 Criteria for discontinuation for each research participant**

If any of the following events occur during the research period, the investigators will discontinue the research on the relevant research participants. When the investigators decide to discontinue or suspend the research, the investigators will take appropriate action to deal with the research participants.

1) If the research participant (or surrogate) asks to discontinue the research.

2) If the research participant discontinues participation in the research for personal reasons (e.g. moving, changing doctor or hospital, busy schedule, inability to follow up, etc.)

3) If the research participants are found to be unsuitable for the subjects after the start of the research

4) If an accidental incident occurs

5) If an adverse event occurs (including exacerbation of the underlying disease, complications or accidental injury) and the investigator decides that the study should be discontinued

6) If it becomes difficult to continue the research due to ill health

7) When there is a serious deviation from the research protocol and it is judged that the research cannot be evaluated

8) When it is found that the research participant is not carrying out the task as instructed by the investigators

9) In other cases where the investigators judge that it is difficult to continue the research and that discontinuation is appropriate.

［Rationale]

This criterion was set in order to ensure the ethical and safe implementation of the research and to ensure the safety of the research participants.

[Methods of action at the time of discontinuation]

After discontinuation, observation will not be continued.

1. **Medical treatment of the clinical research participants**

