**9.5** **The observation period for participants in the study after the incidence of disease, etc.**

Research subjects after an outbreak of disease, etc., are followed up until the disease, etc., disappears or until the principal investigator (co-)investigator decides that it is no longer necessary.

1. **Statistical analysis**

If the statistical analysis plan is changed from that established within the protocol, the research protocol should be revised.

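### Participants discontinued for not performing the task are no longer observed, so outcomes are lost selectively in the app arm, completely for MoCA-J and SF-36

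*Protocol*

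**What the plan says.** Protocol section 6.4 lists nine events on which the investigators will discontinue a participant. Criterion 8 reads "When it is found that the research participant is not carrying out the task as instructed by the investigators". It gives no threshold or duration. The section closes, for all nine criteria alike, with "After discontinuation, observation will not be continued".

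Other passages bear on this:

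- **Arms (5.3).** Participants are "allocated in a 1:1 ratio to the SoroTouch treatment group and the non-treatment group".
- **Task (5.2.2).** "The participants will try to complete each stage, which has 30 missions, three aspects in 30 minutes each day". Staff check the logged learning time and mission completion.
- **Low use (5.2.2, repeated in 10.6).** "If there are participants whose average daily learning time is less than 10 minutes, the data will be analyzed only for the periods" in which they exceeded 10 minutes. Section 10.6 adds that all evaluated data should nevertheless be used.
- **Assessment times (5.2.2 schedule, 10.5.3, 10.6).** CogEvo is measured at baseline and monthly to month 6. MoCA-J and SF-36 are measured at baseline and month 6 only.
- **Efficacy set (10.1.1).** All randomised, except those with no intervention or no post-intervention assessment.
- **Missing data.** Section 10.5.2 carries the last CogEvo value forward. Section 10.4 says that in principle missing values are not filled in.
- **After an adverse event.** Criterion 5 of 6.4 covers the case "If an adverse event occurs (including exacerbation of the underlying disease, complications or accidental injury) and the investigator decides that the study should be discontinued". Section 9.5 says that participants who develop a disease "are followed up until the disease, etc., disappears or until" the investigator judges follow-up unnecessary.

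**The concern.** Section 6.4 makes ending task participation and ending outcome measurement a single act. Criterion 8 can in practice be triggered only in the app arm, and what triggers it is poor engagement. Whether an outcome is observed then depends on the allocated arm and on behaviour after randomisation, which may be related to the outcome. Randomisation no longer protects the comparison of those who remain, and no analysis can recover values that were never collected.

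Sections 8.2.1 and 8.2.2 call the intervention effective on a statistically significant group difference, and 10.2 intends the results to inform a larger study. A distorted difference would affect both. The target of 20 equals the number of analysed subjects in the sample-size rationale and is also the institution's maximum, so there is no allowance for loss.

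**Working it through.** **1. The plan's own figure.** Inputs from 10.2: effect size 1.4 on CogEvo change, type 1 error 0.05, type 2 error 0.2, 20 analysed. The sidedness is not stated; two-sided is assumed. For a t-test with arms n1 and n2, the noncentrality is 1.4 / √(1/n1 + 1/n2) on n1 + n2 − 2 degrees of freedom. With 9 per arm the power is 0.796. With 10 per arm the noncentrality is 1.4 / √0.2 = 3.13 and the power is 0.841. Ten per arm is the smallest size that reaches 0.80, so the figure of 20 reproduces, with nothing spare.

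**2. What is lost, by endpoint, when criterion 8 is met before month 6.**

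| Endpoint | Post-baseline data if stopped early | Treatment in the analysis |
| --- | --- | --- |
| MoCA-J, SF-36 | None | No value to compare at month 6 |
| CogEvo, stopped after at least one monthly test | Values up to stopping | Stays in the efficacy set; last value carried forward (10.5.2) |
| CogEvo, stopped before the first monthly test | None | Leaves the efficacy set (10.1.1) |

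**3. Complete-case bias for MoCA-J and SF-36.** Let p be the fraction of the app arm lost and δ the gap, in SD, between those retained and those lost. The full-arm mean is (1 − p) × retained + p × lost, so the retained mean exceeds it by p × δ. Neither p nor δ is in the protocol; both are assumptions.

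| Lost of 10 | δ = 0 | δ = 0.5 SD | δ = 1.0 SD |
| --- | --- | --- | --- |
| 2 | 0 | 0.2 × 0.5 = 0.10 | 0.2 × 1.0 = 0.20 |
| 3 | 0 | 0.3 × 0.5 = 0.15 | 0.3 × 1.0 = 0.30 |

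**4. Cross-check by simulation.** In 200,000 trials of 10 per arm with no true effect, the least adherent app participants were dropped. Adherence had an assumed correlation ρ with the outcome.

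| ρ | Lost | Bias (SD) | Two-sided rejection at 0.05 |
| --- | --- | --- | --- |
| 0 | 2 | 0.001 | 0.0486 |
| 0 | 3 | −0.001 | 0.0490 |
| 0.3 | 2 | 0.095 | 0.0556 |
| 0.3 | 3 | 0.138 | 0.0587 |
| 0.5 | 2 | 0.158 | 0.0646 |
| 0.5 | 3 | 0.228 | 0.0745 |

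These lie in the same range as step 3 and vanish when adherence and outcome are unrelated.

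**5. CogEvo power if missing values are not imputed (the 10.4 reading).** With 8 against 10, the noncentrality is 1.4 / √0.225 = 2.95 and the power 0.791. With 7 against 10, it is 1.4 / √0.2429 = 2.84 and the power 0.757. Under 10.5.2 the comparison stays at 10 against 10 for anyone with at least one monthly value, and these two figures do not apply.

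**6. The passages side by side.** A participant averaging under 10 minutes a day, against a 30-minute task, may fall under criterion 8 and also under the low-use rule. Criterion 8 ends observation; the low-use rule says how that person's data are analysed. Nothing says which governs. Separately, a participant discontinued for an adverse event is no longer observed under 6.4 but is followed to resolution under 9.5.

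**The case against.** The strongest reply is that the stated primary analysis largely keeps these people. CogEvo is monthly, one post-baseline value is enough for the efficacy set, and 10.5.2 fills the rest. A reader might infer from the discontinuation rule that the primary comparison shrinks to 7 or 8 against 10, with power of 76% to 79%. The protocol does not support that as the primary analysis: it follows only if 10.4 overrides 10.5.2. Nor can those figures be moved to MoCA-J or SF-36, because the effect size of 1.4 is given for CogEvo change alone. This part of the reply stands. It does not restore the lost CogEvo values. A carried-forward score may cut off later gains or hide a later decline, so it can bias in either direction.

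It is also fair to say that the low-use rule is an analysis rule. A reader might take it as an instruction to keep such people under observation, and so as a flat contradiction of 6.4. It does not say that, and it could be applied to data gathered before discontinuation. What remains is an overlap with a criterion that has no threshold.

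The mismatch with 9.5 disappears if 6.4 means efficacy observation only, since 9.5 is the specific safety rule. But 6.4 does not say so.

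Finally, the trial is exploratory and small. That limits what the results can claim, but not the value of collecting outcomes already scheduled.

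**Conclusion.** The point holds for criterion 8. As written, 6.4 removes outcomes selectively from the app arm in relation to poor engagement. The loss is complete for MoCA-J and SF-36. For CogEvo it is partial and masked by carry-forward under 10.5.2, which itself conflicts with 10.4.

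The size is conditional. With 2 to 3 of 10 lost and a deficit of 0.5 to 1.0 SD, both assumed, the complete-case bias on MoCA-J or SF-36 is 0.10 to 0.30 SD in favour of the app. With no link between adherence and outcome it is zero, and only precision is lost. A reader might infer an established bias towards the app on the primary outcome; the documents do not support this, since the direction for CogEvo is undetermined. The other discontinuation criteria can arise in either arm, so the selective mechanism should not be attributed to them.

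The overlap with the under-10-minute rule and the mismatch with 9.5 are gaps in wording that need reconciling. Neither is further evidence of bias.

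**What to change.** In 6.4, separate the end of outcome observation from non-performance of the task. Possible wording: *Participants who meet criterion 8 continue the scheduled CogEvo assessments and the month-6 MoCA-J and SF-36 unless they withdraw consent, and are analysed in their allocated arm.* The sentence is limited to criterion 8 on purpose. Extending it to every reason except withdrawn consent would reach participants stopped for ill health, unsuitability or an adverse event, which this point does not address.

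Also:

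- State how criterion 8 and the under-10-minute rule in 5.2.2 and 10.6 relate, and which governs when both apply.
- Reconcile the closing sentence of 6.4 with 9.5 on follow-up after an adverse event.
- Reconcile 10.4 with 10.5.2 on missing CogEvo values.

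No view is taken on when app use or participation should stop. The cost is protocol wording and a few assessments already on the schedule, with no new procedure. The change has to be made before participants are discontinued, because the missing values cannot be collected later.
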